**Table 7 T7:** 

Safety follow-up
• Vital signs and ECOG status • Physical examination • Laboratory tests: Hematology panel, chemistry panel, including also TSH, fT3/fT4 • C-lab blood sampling (20ml) for tumor-DNA • Pembrolizumab infusion is continued according to SmPC at the discretion of the physician • Assessment of adverse events, concomitant therapies and subsequent anti-cancer therapies

### Sample collection for biomarker program

2.6

Blood samples for immune analysis (**Table 8**) will be collected at visit 1, 5, 6, 8 (EOT) as well as at safety follow-up (FU), FU1, FU2 and at PD (**Figure 2**).

**Table 8 T8:** 

Translational work-up
• Immunohistochemistry (IHC) for PD-L1 to deduce tumor proportion score (TPS), immune cell (IC) score and combined positivity score (CPS), and IHC for telomerase tissue expression • Next-generation T cell receptor repertoire sequencing of circulating and tumor-infiltrating lymphocytes (TiL) • Next-generation gene panel sequencing for mutational profiling of tumor or circulating tumor DNA (ctDNA, liquid biopsy) • In individual patients liquid biopsy courses will be confirmed with digital droplet PCR (ddPCR) as an alternative methodology • Immune response assays against hTERT peptides measured by 3H-Thymidine proliferation and IFNgamma ELISPOT assays

In centers with expertise in collecting and locally freezing peripheral blood mononuclear cells (PBMCs), additional blood will be collected at visit 1, 6 and at PD from patients receiving UV1 vaccination (from patients of both arms only at site 01 Halle only) for immune response assays (**Table 8**).

Tumor tissue acquired before treatment initiation at first diagnosis or at relapse (biopsy of primary tumor, surgical material, or biopsy material of metastatic lesions) and potential biopsy or surgical material acquired during the study will be analyzed (**Table 8**, **Figure 2**).

Fecal samples will be collected prior to treatment to evaluate the gut microbiome (**Table 8**).

### Analysis of primary study endpoint

2.7

The primary study endpoint progression PFS@6 will be analyzed as the proportion of all intention-to-treat patients being known to be alive without progression at 6 months after randomization, providing the 95%, 90% and 80% confidence intervals for this estimate.

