### Treatment

2.3

Eligible patients (**Table 1**) will be randomized to either pembrolizumab, Arm A, about 25 patients, or pembrolizumab in combination with UV1 vaccination plus sargramostim (GM-CSF) as an adjuvant, Arm B, about 50 patients (**Figure 2**).

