### Sample size estimation

2.9

The progression-free survival rate after 6 months (PFSR@6) with single agent pembrolizumab as first-line treatment in R/M HNSCC is about 25%. Pembrolizumab in combination with UV1 vaccination should result in a PFSR@6 of 40% to be regarded as promising for further development in a phase III setting. Based on these assumptions and by applying a one-sided test with an alpha error level of 0.1 and a beta error of 0.2 (corresponding to a power of 80%), 46 evaluable patients are needed in the experimental arm. According to the 2:1 randomization, about 23 patients will be included in the control arm. To allow for a 10% drop out rate, a total of 75 patients should be included.

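### The 80% power is computed for 46 evaluable patients, but the primary analysis keeps all randomised patients and counts unknown status as failure; power under that rule lies between about 67% and 84%

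*Protocol article*

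**What the plan says.** - **Sample size estimation (2.9).** The 6-month progression-free rate "with single agent pembrolizumab as first-line treatment in R/M HNSCC is about 25" per cent, and the combination "should result in a PFSR@6 of 40% to be regarded as promising". With a one-sided alpha of 0.10 and power of 80%, "46 evaluable patients are needed in the experimental arm". The control arm follows from the allocation ratio: "According to the 2:1 randomization, about 23 patients will be included in the control arm". Then: "To allow for a 10% drop out rate, a total of 75 patients should be included".
- **Treatment (2.3).** The planned size of the experimental group is "Arm B, about 50 patients".
- **Analysis of primary study endpoint (2.7).** The estimate is the "proportion of all intention-to-treat patients being known to be alive without progression at 6 months after randomization", reported with 95%, 90% and 80% confidence intervals.
- **Statistics and data handling (2.8).** The arms are not formally compared. Further development rests on the primary endpoint and its interval, the control-arm findings, and safety and feasibility.

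**The concern.** An allowance for drop-out restores power only if drop-outs are removed from the analysis and the added patients take their place. Section 2.9 reasons in this way: 46 evaluable patients, then more to cover losses. Section 2.7 has no evaluable set. Its denominator is every randomised patient, and a success must be *known*, so a patient whose 6-month status is missing is a non-success. Under that rule the added patients enlarge the denominator, but each loss also lowers the expected success rate.

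A reader will take 80% as the power of the section 2.7 analysis. If it is lower, the chance that a combination with a true 40% rate falls short of the design threshold exceeds the planned 20%. That threshold feeds a decision about phase III.

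**Working it through.** **Inputs.** Reference rate 0.25, target 0.40, one-sided alpha 0.10, power 0.80, 46 evaluable patients and 10% drop-out (section 2.9); about 50 patients in Arm B (section 2.3); all randomised patients analysed, with unknown status not a success (section 2.7). Because the arms are not formally compared (section 2.8), the design test is a single-arm test against 25%.

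**Formula.** P(X ≥ r | n, p) = Σ from k = r to n of C(n,k) p^k (1−p)^(n−k). The cut-off r is the smallest value with P(X ≥ r | n, 0.25) ≤ 0.10. Power is P(X ≥ r | n, p) at the expected success rate p.

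**Step 1: the plan's own figure.** For n = 46, r = 16:
- P(X ≥ 16 | 46, 0.25) = 0.0896
- P(X ≥ 16 | 46, 0.40) = 0.808

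This is the smallest n that meets both limits (n = 43 gives power 0.799, n = 45 gives 0.775). The 46 is reproduced.

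**Step 2: the cut-off for the section 2.7 denominator.** For n = 50, r = 17, with P(X ≥ 17 | 50, 0.25) = 0.0983. The article states no such cut-off; it follows from the stated alpha. It also matches the reported 80% interval: the exact lower bound first exceeds 0.25 at 16/46 (0.254) and at 17/50 (0.2506).

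**Step 3: power when unknown status counts as failure.** Let d be the share with unknown 6-month status, unrelated to outcome. If 40% is the rate among evaluable patients, the expected success rate is 0.40 × (1 − d). The last column uses 0.25 × (1 − d).

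| d | Expected rate at a true 40% | Power at 17/50 | Rejection rate at a true 25% |
|---|---|---|---|
| 0% | 0.400 | 84.4% | 9.8% |
| 2% | 0.392 | 81.5% | 8.4% |
| 5% | 0.380 | 76.5% | 6.6% |
| 8% | 0.368 | 70.8% | 5.1% |
| 10% | 0.360 | 66.6% | 4.2% |

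At d = 4% power is 78.2%, already below 80%.

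**Step 4: a fixed number lost.**
- 4 of 50 lost, leaving the planned 46: P(X ≥ 17 | 46, 0.40) = 71.4%
- 5 of 50 lost: P(X ≥ 17 | 45, 0.40) = 67.3%

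**Step 5: other readings of the two rates.**
- Both rates diluted by 10%: 0.25 × 0.90 = 0.225 and 0.40 × 0.90 = 0.36. The cut-off becomes 16/50 (alpha 0.079) and exact power is 76.7%.
- Both rates already count unknown status as failure: no dilution applies, and power at n = 50 is 84.4%.

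**Step 6: what full compensation would take.** First reaching 80% exact power for 36% against 25% needs 81 patients in Arm B, against about 50 planned.

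**The case against.** A reader might infer that the trial simply has 67% power. The documents do not support that as a flat statement, because it needs three things that the article does not settle:

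1. *All drop-outs have unknown 6-month status.* Drop-out is not defined. Under Follow-up (2.5), all patients are evaluated every 3 months after end of treatment, and disease status comes from routine imaging, so stopping treatment does not by itself make status unknown. A patient lost after documented progression costs nothing.
2. *The 40% is a rate among evaluable patients.* Section 2.9 does not say so. The opposite reading gives 84%, although the 10% allowance would then have no purpose.
3. *The 25% benchmark is free of the same dilution.* Section 2.9 does not say how missing status was handled in it.

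A reader might also infer that an effective combination would be discarded. The article describes an estimation design with no stated cut-off. The decision also draws on the control arm, which is analysed by the same rule, so similar losses would lower both estimates and show up in the calibration arm. With about 25 controls that signal is imprecise, so it offsets the bias only in part.

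It may also be said that, without a formal comparison, power does not matter. Only the comparison between arms is ruled out. Section 2.9 itself sizes the trial on a one-sided test, and the 80% interval reproduces its cut-offs.

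Finally, the absence of a Kaplan–Meier sensitivity analysis is no fault here, since such analyses are commonly left to the analysis plan. What stands after all this is the mismatch between sections 2.7 and 2.9.

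**Conclusion.** The concern holds in conditional form. The 80% was derived for an evaluable set that the primary analysis does not use. On the article's own inputs, power under the section 2.7 rule ranges from about 67% to 84%. The lower end requires the full 10% to have unknown status unrelated to outcome, 40% to be a rate among evaluable patients, and an undiluted 25%. At that end the false-negative risk is about 33% (1 − 0.666) instead of 20%.

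The error is conservative: it does not inflate the false-positive rate, which falls to about 4% at a true 25% with 10% unknown. The endpoint, denominator and handling of unknown status in section 2.7 are clear and defensible; the power statement is what needs correcting. This should be fixed, but it does not undermine the design.

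**What to change.** Keep the section 2.7 definition unchanged. In section 2.9:

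- Delete *evaluable*, and say that drop-out here means unknown 6-month status, if that is what is intended.
- State whether 25% and 40% are rates with unknown status counted as failure.
- Replace the flat 80% by the power for n = 50 under that rule across 0 to 10% unknown status. If 40% is a rate among evaluable patients and 25% is unchanged, this is 84% at 0%, 76.5% at 5% and 67% at 10%. If both are already rates with unknown status as failure, it is 84%.

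A Kaplan–Meier 6-month estimate, with patients of unknown status censored, is an optional sensitivity analysis that would help separate loss to follow-up from lack of effect.

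The cost is a few sentences and, on most readings, a less favourable stated power. No extra patients are needed, provided that the lower power is accepted openly.

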### Statistics and data handling

2.8

The FOCUS trial is designed as a randomized phase II study to estimate the therapeutic effectiveness of pembrolizumab in combination with UV1 vaccination in relation to the standard treatment (single drug pembrolizumab). The assumptions on outcome after standard therapy is derived from available data and controlled for by a randomized reference (or calibration) arm. Due to this design, analysis of both treatment arms but no formal statistical comparison will be performed. All secondary endpoint analyses are considered explorative. Further clinical development of this combination depends on the primary endpoint (and its confidence interval), the findings in the control arm, and the supporting safety and feasibility findings.

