**Objective:**

The FOCUS trial is designed to estimate the effectiveness of UV1 vaccination in combination with pembrolizumab versus pembrolizumab as a single agent in patients with R/M HNSCC.

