### Study objective

2.1

The primary objective of this study is to assess the efficacy of UV1 vaccination in combination with pembrolizumab in patients with R/M HNSCC and PD-L1 CPS ≥1 based on progression free survival according to iRECIST (progression-free survival rate at 6 months after randomization, PFS@6) (15).

Secondary clinical endpoints of this study are overall survival, objective response rate and duration of response according to iRECIST. Other secondary objectives are the UV1 vaccine induced immune responses and the clearance rate of ctDNA from blood during treatment. Additionally, this study will explore the safety and tolerability of UV1 vaccination in combination with pembrolizumab according to NCI CTCAE v5.0. Other objectives are the exploration of what patient subgroups benefit most from this combined approach and the establishment of liquid biopsy tumor monitoring in HNSCC.

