**Table 1 T1:** 

Inclusion criteria
• Males and Females who are at least 18 years of age • Histologically confirmed diagnosis of a non-resectable recurrent or metastatic head and neck squamous cell carcinoma (not necessarily reconfirmed at time of enrolment) • At least one measurable tumor lesion as per RECIST v1.1, (scan not older than 4 weeks before randomization) • Eligible for pembrolizumab monotherapy (PD-L1 CPS ≥1 and adequate laboratory parameters for pembrolizumab monotherapy as assessed by the investigator) • ECOG-performance score 0-2 • Written informed consent obtained according to international guidelines and local laws • Ability to understand and give informed consent • Safe contraception measures for males and females. Procedures with a pearl index of less than 1% apply as safe pregnancy prevention measures

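### The aim is stated as UV1 plus pembrolizumab versus pembrolizumab, but no between-arm difference in PFS@6 is named, and the stated alpha and power hold only against a fixed 25%

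*Protocol article*

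**What the plan says.** The Abstract (Objective), repeated at the end of the Introduction, describes the trial as "designed to estimate the effectiveness of UV1 vaccination in combination with pembrolizumab versus pembrolizumab as a single agent in patients with R/M HNSCC". Section 2.8 likewise sets the aim in relation to standard treatment. Section 2.1 words it without a comparator: the "primary objective of this study is to assess the efficacy of UV1 vaccination in combination with pembrolizumab".

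Section 2.7 analyses PFS@6 as a proportion of intention-to-treat patients, "providing the 95%, 90% and 80% confidence intervals for this estimate". It names no difference between arms.

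Section 2.8 says the assumption about standard therapy is "controlled for by a randomized reference (or calibration) arm", and then: "Due to this design, analysis of both treatment arms but no formal statistical comparison will be performed". It adds that further development will depend on the primary endpoint and its interval, on what is seen in the control arm, and on safety and feasibility. It gives no quantity or rule for weighing the control arm.

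Section 2.9 takes the 6-month rate "with single agent pembrolizumab as first-line treatment in R/M HNSCC is about 25" per cent and asks for 40% with the combination. With a one-sided alpha of 0.10 and 80% power, this gives 46 evaluable patients in arm B. Arm A gets about 23 through the 2:1 allocation.

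**The concern.** A randomized arm can protect against a wrong assumption about the control rate only if the two arms are brought together in some way. Here the text claims that protection but names no estimate that uses both arms. Two separate proportions, each with its own interval, do not give an interval for their difference, which is the quantity the stated aim asks for.

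The error rates in section 2.9 are conditional on an approximate 25%. If pembrolizumab alone does somewhat better than that in the recruited patients, arm B can look promising even though the vaccine adds nothing. The Introduction itself reports that pembrolizumab efficacy rises with PD-L1 expression, and eligibility spans all CPS values of 1 or more and "ECOG-performance score 0-2". The control rate will therefore depend on who is enrolled. At stake is a phase III decision that rests partly on an unchecked constant.

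**Working it through.** **Inputs.** From section 2.9: p0 = 0.25, p1 = 0.40, one-sided alpha 0.10, power 0.80, 46 evaluable in arm B and about 23 in arm A. From section 2.3: about 50 and 25 randomized. True pembrolizumab rates other than 25% are assumptions, because the article gives no range.

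**1. Reproducing the 46.** For each n, take the smallest r with P(X ≥ r | n, 0.25) ≤ 0.10, then require P(X ≥ r | n, 0.40) ≥ 0.80 (exact binomial).
- n = 45: r = 16, alpha 0.0753, power 0.7751. Not enough.
- n = 46: r = 16, alpha 0.0896, power 0.8078. This is the smallest n that meets both limits.

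The 46 is therefore an exact one-sample test of arm B against 25%. Equivalently, 16/46 is the first count whose exact 80% interval has a lower limit above 25% (0.2538; for 15/46 it is 0.2342). A 2:1 two-arm test at the same alpha and power would need 66 + 132 patients, so arm A plays no part in this calculation.

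**2. Sensitivity to the 25%.** With UV1 inactive, both arms share the true rate p. The chance that arm B alone crosses the bar is P(X ≥ r | n, p):

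| True rate p | n = 46, r = 16 | n = 50, r = 17 |
|---|---|---|
| 20% | 1.4% | 1.4% |
| 25% | 9.0% | 9.8% |
| 28% | 19.3% | 21.3% |
| 30% | 28.7% | 31.6% |
| 35% | 56.8% | 61.1% |

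A 5-point error in the assumption roughly triples the risk at n = 46 (28.7 / 9.0 = 3.2).

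**3. Can arm A, read separately, reveal the error?** With 25 patients at 25%, SE = √(0.25 × 0.75 / 25) = 0.0866, and 1.96 × 0.0866 = 17 points. An observed 6/25 (24%) has an exact 95% interval of 9.4% to 45.1%. Such a reassuring result (6 or fewer of 25) still occurs in 34% of trials if the true rate is 30%, and in 17% if it is 35%.

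**4. How much the use of arm A matters.** The rules below are illustrations with 46 versus 23 patients; none is in the protocol. Each row adds a condition to the arm B bar.

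| Go requires at least 16/46 in arm B and | False go at 25% | at 30% | at 35% | Power, 40% vs 25% |
|---|---|---|---|---|
| nothing more | 9% | 29% | 57% | 81% |
| observed B above A | 8% | 22% | 36% | 76% |
| 80% CI (Wald) for B − A above 0 | 4% | 8% | 10% | 48% |

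At a true 30%, the false-go risk runs from 8% to 29% across these rules, and the stricter use of arm A costs much of the power.

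**5. Precision of the difference.** At 40% versus 25% with 50 and 25 patients, SE = √(0.25 × 0.75 / 25 + 0.40 × 0.60 / 50) = √(0.0075 + 0.0048) = 0.111. Half-widths are 1.2816 × 0.111 = 14 points (80%), 1.645 × 0.111 = 18 points (90%) and 1.96 × 0.111 = 22 points (95%). With 46 and 23, SE = 0.116 and the half-widths are 15, 19 and 23 points. A one-sided 0.10 test of the difference would have about 48% power (23 vs 46) to 50% power (25 vs 50).

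**The case against.** A calibration arm without a formal comparison is an accepted phase II design, and section 2.8 discloses it. With power near 50%, a hypothesis test between arms would decide little. This stands: leaving out the test is not an error.

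A reader might infer that arm A is not used at all. The documents do not support that, because section 2.8 lists control-arm findings among the things the development decision rests on. What is missing is any stated quantity that links the arms.

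A reader might also infer that a small error in the 25% produces a false go. It does not. At a true 30% the risk rises from about 9% to 29%, and only if the decision rests on arm B alone. The bar of 16/46 is implied by the sample-size test and is not written as a decision rule. With a strict use of arm A the risk at 30% would be about 8%.

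Section 2.8 excludes a formal comparison, not a descriptive difference with an interval, and the unseen analysis plan may contain one. That is fair, and it keeps this from being a claim of omission. But the article itself fixes the primary analysis, the one-sample sizing and the claim that arm A controls the assumption, and these three do not fit together as written.

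Finally, the article does not describe the population behind the 25%. Case mix could move the true rate down as well as up, and ECOG 2 patients might lower it. A lower rate would reduce the false-go risk (1.4% at 20%) but also make an active vaccine harder to recognise against a fixed 25%.

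**Conclusion.** The point holds as a mismatch between aim and stated analysis. It is an inexpensive improvement and does not invalidate the design. The aim is comparative in the Abstract, the Introduction and section 2.8, the sizing is purely one-sample, and no between-arm quantity is named. The stated alpha of 0.10 and power of 80% apply only if 25% is right. With UV1 inactive and arm B read alone at n = 46, the chance of crossing the bar is 19%, 29% or 57% at true rates of 28%, 30% or 35%. Those rates are assumptions, and the figures are the case in which arm A does not influence the decision. Saying that arm A controls for the assumption is more than 23 to 25 patients read separately can deliver.

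**What to change.** In sections 2.7 and 2.8, keep the statement that no formal hypothesis test between arms is planned, and add: *The difference in PFS@6 (arm B minus arm A) will be estimated with 80%, 90% and 95% confidence intervals (for example Newcombe or Miettinen-Nurminen), and the decision on further development will be read together with this estimate.*

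Replace the wording that the assumption is controlled for by arm A with a statement that the alpha of 0.10 and the power of 80% apply only against a fixed 25%. Show the operating characteristics for control rates of 20% to 35%, as in the first table above.

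The cost is two sentences and one table, with no further patients, visits or data. The downside is that the interval for the difference will be visibly wide: about ±14 to 15 points at 80% and ±22 to 23 points at 95%. Those making the phase III decision should see that width.

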### Sample size estimation

2.9

The progression-free survival rate after 6 months (PFSR@6) with single agent pembrolizumab as first-line treatment in R/M HNSCC is about 25%. Pembrolizumab in combination with UV1 vaccination should result in a PFSR@6 of 40% to be regarded as promising for further development in a phase III setting. Based on these assumptions and by applying a one-sided test with an alpha error level of 0.1 and a beta error of 0.2 (corresponding to a power of 80%), 46 evaluable patients are needed in the experimental arm. According to the 2:1 randomization, about 23 patients will be included in the control arm. To allow for a 10% drop out rate, a total of 75 patients should be included.

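### Minor: 75 randomized patients cover about 8% drop-out on the protocol's own figures, not the stated 10%

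*Protocol article*

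**What the plan says.** Section 2.9 (Sample size estimation) plans for a 6-month progression-free rate of 25% with pembrolizumab alone. The combination "should result in a PFSR@6 of 40% to be regarded as promising". The test is one-sided, with alpha 0.10 and power 80%. From this the section concludes that "46 evaluable patients are needed in the experimental arm". It continues: "According to the 2:1 randomization, about 23 patients will be included in the control arm". The last step is: "To allow for a 10% drop out rate, a total of 75 patients should be included".

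Section 2.2 (Study design) repeats the total of 75. Section 2.3 (Treatment) splits it approximately 2:1, with about 25 patients in Arm A and, for the combination, "Arm B, about 50 patients".

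Two other sections bear on the reading. Section 2.7 takes as denominator all intention-to-treat patients and counts as successes only those known to be alive and progression-free at 6 months. Section 2.8 says that the control arm serves as a reference and that the arms are not formally compared.

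**The concern.** Section 2.9 fixes four figures: 46 evaluable patients in the experimental arm, about 23 controls, a 10% allowance and a total of 75. Once three are set, the fourth follows, and the printed one differs. If 10% of patients are lost, the experimental arm falls below the number that the section says it needs. What is at stake is the accuracy of the sample-size statement. A reader who checks it will find that the allowance does not deliver the 46.

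**Working it through.** **Inputs.** From section 2.9: p0 = 0.25, p1 = 0.40, one-sided alpha 0.10, power 0.80, 46 evaluable in the experimental arm, about 23 controls, 10% drop-out, total 75. From section 2.3: about 50 and about 25 randomized. From section 2.7: intention-to-treat denominator.

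**Step 1. Reproduce the 46.** For each n, take the smallest r with P(X ≥ r | n, 0.25) ≤ 0.10. Power is then P(X ≥ r | n, 0.40). The smallest n with power of at least 80% is n = 46, with r = 16, alpha 0.0896 and power 80.8%. Other methods give other numbers: normal approximation 42, arcsine 44, continuity correction 49. The 46 is therefore reproduced by an exact binomial calculation, although the document does not name the test.

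**Step 2. Check the allowance.**
- Evaluable total: 46 + 23 = 69.
- Strict inflation: 69/0.9 = 76.7, so 77. The experimental arm alone needs 46/0.9 = 51.1, so 52. Rounding up each arm separately gives 52 + 26 = 78.
- Simply adding 10%: 69 × 1.1 = 75.9, so 76.
- After 10% loss from the planned numbers: 50 × 0.9 = 45; 25 × 0.9 = 22.5; 75 × 0.9 = 67.5.
- Loss that 75 does cover: 1 − 69/75 = 0.08. For the experimental arm, 1 − 46/50 = 0.08.

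Neither usual convention, rounded up, gives 75.

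**Step 3. What the missing evaluable patient means for power.** Exact one-sided test, 25% against 40%:

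| Evaluable n | r | Alpha | Power |
|---|---|---|---|
| 43 | 15 | 0.096 | 79.9% |
| 44 | 16 | 0.063 | 73.9% |
| 45 | 16 | 0.075 | 77.5% |
| 46 | 16 | 0.090 | 80.8% |
| 47 | 17 | 0.059 | 75.1% |
| 48 | 17 | 0.070 | 78.6% |
| 49 | 17 | 0.084 | 81.6% |
| 50 | 17 | 0.098 | 84.4% |

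Power moves in a saw-tooth, because r must be a whole number. Going from 46 to 45 costs 3.3 points, but going from 46 to 47 costs 5.7. If each patient independently drops out with probability 10%, average power is 77.3% with 50 randomized and 78.6% with 52. The strictly inflated number gains 1.3 points and still does not reach 80%.

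**Step 4. Power on the section 2.7 denominator.** With n = 50, r = 17 and alpha 0.0983:
- If the success rate among all intention-to-treat patients is 40%, power is 84.4%.
- If, as an assumption, 10% are lost regardless of outcome and count as non-successes, the rate is 0.40 × 0.9 = 0.36. Power is then 66.6%, with the reference rate kept at 25%.

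**The case against.** The strongest reply is that this is rounding. The arm sizes are given as approximate, 69 × 1.1 = 75.9 lies close to 75, and 75 divides exactly 2:1. The shortfall against 77 is two patients, with one evaluable patient missing in the experimental arm. The half patient missing in the control arm has no effect on power, because the arms are not formally compared. This stands, and it is why the point is minor. It does not make the sentence right: the total of 75 carries no such qualifier, and an allowance for loss is normally rounded up.

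A reader might also infer that the trial has 77.5% power where 80% is claimed. The documents do not support that, for three reasons:
- Section 2.7 keeps drop-outs in the denominator, so the planned primary analysis has about 50 patients, not 45.
- The step from 80.8% to 77.5% mostly reflects the discreteness of the exact test. One patient more than required, 47, gives only 75.1%.
- Section 2.9 mentions only a one-sided test. An exact test is likely, since it reproduces the 46. By normal approximation the power at 45 would be 82.2%, although that method would have asked for 42 patients, not 46.

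Section 2.8 also bases further development on the estimate and its confidence interval, the control-arm findings, and safety and feasibility. No decision rule of 16 out of 45 is stated.

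**Conclusion.** The sentence is wrong as written, and the error is minor. On the figures of section 2.9 and the split in section 2.3, 75 patients allow for about 8% drop-out; 10% loss leaves 45 evaluable patients in the experimental arm against 46 required, and strict inflation gives 77. This part needs only the printed numbers, with the approximate arm sizes read as 50, 25 and 23.

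The power figures need more. The 77.5% assumes an exact binomial test and an analysis of evaluable patients only. The 84.4% and 66.6% assume the same test on 50 intention-to-treat patients, and differ in whether losses lower the success rate. None of them can be put forward without its label as the power of the trial. No conclusion about the treatment, the number recruited or the planned analysis changes.

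**What to change.** Keep 75 and correct the allowance in section 2.9. Suggested wording: *A total of 75 patients (about 50 and 25) allows for a drop-out rate of about 8%, leaving 46 of 50 evaluable in the experimental arm.*

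Do not add 77% as the trial's power. If a power under 10% loss is wanted, name the test and the analysis set. Give 77.5% for an exact one-sided binomial test in 45 evaluable patients. Beside it, give the values for the intention-to-treat analysis of section 2.7 with 50 patients: 84.4% at a success rate of 40%, and 66.6% if the 10% lost are assumed to be non-successes (36%).

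The cost is one corrected figure, plus one sentence if power is reported. Recruitment does not change.
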